# Effect of low-load resistance training with different degrees of blood flow restriction in patients with knee osteoarthritis: study protocol for a randomized trial

**DOI:** 10.1186/s13063-021-05946-7

**Published:** 2022-01-03

**Keywords:** Knee osteoarthritis, Blood flow restriction, Vascular occlusion, Resistance training, Rehabilitation

## Abstract

**Background:**

Knee osteoarthritis (KOA) is a common degenerative disease that causes pain, functional impairment, and reduced quality of life. Resistance training is considered as an effective approach to reduce the risk of muscle weakness in patients with KOA. Blood flow restriction (BFR) with low-load resistance training has better clinical outcomes than low-load resistance training alone. However, the degree of BFR which works more effectively with low-load resistance training has not been determined. The purpose of this study is to evaluate the effectiveness of different degrees of BFR with low-load resistance training in patients with KOA on pain, self-reported function, physical function performance, muscle strength, muscle thickness, and quality of life.

**Methods:**

This is a study protocol for a randomized, controlled trial with blinded participants. One hundred individuals will be indiscriminately assigned into the following groups: two training groups with a BFR at 40% and 80% limb occlusion pressure (LOP), a training group without BFR, and a health education group. The three intervention groups will perform strength training for the quadriceps muscles twice a week for 12 weeks, while the health education group will attend sessions once a week for 12 weeks. The primary outcome is pain. The secondary outcomes include self-reported function, physical function performance, muscle strength of the knee extensors, muscle mass of the quadriceps, quality of life, and adverse events. Intention-to-treat analysis will be conducted for individuals who withdraw during the trial.

**Discussion:**

Previous studies have shown that BFR with low-load resistance training is more effective than low-load resistance training alone; however, a high degree of BFR may cause discomfort during training. If a 40% LOP for BFR could produce similar clinical outcomes as an 80% LOP for BFR, resistance training with a low degree of BFR can be chosen for patients with KOA who are unbearable for a high degree of BFR.

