It has shown in previous studies that the effectiveness of BFR with LLRT is not conclusive compared with LLRT alone [26]. For instance, Ferraz et al. demonstrated that LLRT with BFR is more effective in relieving pain compared with LLRT alone [22], while another study suggested that there was no difference between the two approaches [19]. Therefore, in this study, we set a group of LLRT without BFR to investigate whether LLRT with lower LOP is more effective than LLRT alone. Due to the fact that health education constitutes a minimized intervention that is nonetheless important for KOA [27], we set health education as a control group for comparison with the other three groups. The aim of this study is to investigate the efficacy of LLRT with different degrees of BFR in patients with KOA. Our measures will include pain, self-reported function, physical functional performance, muscular strength, muscle thickness, and QoL. We will also observe any adverse events to verify the safety of BFR training during the study.

Hypotheses:
LLRT, LLRT with low BFR (40% LOP), and LLRT with high BFR (80% LOP) will all be more effective than health education.Both LLRT with 40% BFR and 80% BFR will be more effective than LLRT alone, but there will be no difference between the two levels of BFR.

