### Sample size estimation

Previous studies have shown that the effect size for pain is 0.38–0.49 [52, 53]. The sample size was estimated by using G-Power software (version 3.1.9.6, Heinrich-Heine-Universität Düsseldorf, Düsseldorf, Germany) with the following parameters: analysis of variance (ANOVA) with repeated measures, a type I error of 5% (*α* = 0.05), a power of 95% (*β* = 0.05), group numbers = 4, number of measurements = 3, and effect size = 0.38. The total sample size of this study should be a minimum of 84 participants. With a possible dropout rate of 15%, it is estimated that a sample size of 25 patients per group will be needed to verify our study hypotheses for the primary outcomes.

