## Discussion

BFR training has become a novel intervention for lower limb degeneration or post-surgical musculoskeletal disorders. However, there have been no consistent recommendations for BFR training in treating KOA in any guidelines until now. In this trial, we will investigate the efficacy of LLRT combined with different BFR pressures (0%, 40%, and 80% LOP) on pain, self-reported function, physical functional performance, muscle strength, muscle mass, and QoL.

Although several studies have indicated that BFR combined with LLRT is more effective than LLRT alone [19, 20], the most efficacious degree of BFR has not been determined. If a 40% LOP during BFR will produce similar clinical outcomes as an 80% LOP during BFR in patients with KOA, resistance using a lower LOP can be a good choice for those who are unbearable for high degree of LOP. Additionally, there has been no study comparing the effects of BFR training with a control group without an exercise intervention, and a complete placebo control is not applicable for patients with KOA. Thus, we will set up a control group (the health education group), which will make the study more rigorous and objective. We believe our study will provide evidence for the effectiveness of RT with BFR, which is important for clinicians in treating patients with KOA.

This trial meets the requirements of methodology for the application of randomization, allocation concealment, and ITT approach, as well as masking for patients. In this trial, there will be two sessions per week for 12 weeks, yielding a total of 24 exercise sessions for the exercise intervention groups. We will investigate the short-term effects (12 weeks) of these four groups for all clinical outcomes and safety, as well as the mid-term (24 weeks) effects of pain and self-reported function.

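### The conclusion that low-degree BFR can be chosen rests on 40% and 80% LOP being similar and is not tied to the hypothesis that BFR beats low-load training alone

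*Protocol article*

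**What the plan says.** The practical conclusion appears twice in the protocol article. In the Discussion paragraph of the abstract, if 40% LOP "could produce similar clinical outcomes as an 80% LOP for BFR, resistance training with a low degree of BFR can be chosen" for patients who cannot tolerate a high degree. In the main Discussion, on the same condition, "resistance using a lower LOP can be a good choice for those who are unbearable for high degree of LOP". Similarity of 40% and 80% LOP is the only condition in either place.

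On whether BFR adds anything to low-load training, the article says two things:

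- Abstract, Discussion: "Previous studies have shown that BFR with low-load resistance training is more effective than low-load resistance training alone".
- Background, final paragraph: "the effectiveness of BFR with LLRT is not conclusive compared with LLRT alone". For pain it describes one study that found a benefit and one that found no difference. It then says that the LL arm was included "to investigate whether LLRT with lower LOP is more effective than LLRT alone".

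Hypothesis 2 has two halves: "Both LLRT with 40% BFR and 80% BFR will be more effective than LLRT alone", and "there will be no difference between the two levels of BFR". The Statistical analyses section sets P < 0.05 for all data. The article gives no definition of similar and no margin.

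**The concern.** The patients addressed by the conclusion have a third option within this trial: the same low-load programme with an uninflated cuff. Whether 40% LOP resembles 80% LOP does not say whether 40% LOP is better than that. Similarity is what one would see if both levels work equally well, and equally what one would see if neither adds anything.

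The abstract bridges the gap by treating superiority over low-load training as known, and the main Discussion leans on earlier studies in the same way. The Background does not accept that premise and gives it as the reason for the LL arm. So the article holds the question open, includes an arm to answer it, and then words its conclusion so that the answer is not needed. If BFR added nothing, a reader could still be told that low-degree BFR is a suitable choice.

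This is separate from the familiar problem of reading a non-significant result as equivalence. A sound equivalence margin would not cure it, because two levels that add nothing are truly equivalent.

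**Working it through.** **The plan's own figure.** Sample size estimation gives 4 groups, 3 measurements, effect size f = 0.38, alpha 0.05 and power 95%. With a correlation of 0.5 between measurements (assumed; not stated), the between-groups test has noncentrality f² × N × m / (1 + (m − 1)ρ) = 0.1444 × 84 × 3 / 2 = 18.2 on 3 and 80 df. Its power is 0.952, and at N = 80 it is 0.941, so the stated 84 (21 per arm) reproduces. For dropout, 84 / 0.85 = 98.8, which leads to 4 × 25 = 100. The size was therefore set for an overall between-groups test, not for 40% v LL or 40% v 80%.

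**Inputs for the check.** 25 per arm (21 evaluable after dropout); two-sided 0.05 (sidedness not stated, so assumed); t contrasts with variance pooled over four arms. The article gives no VAS SD; 20 mm is assumed, with 15 and 25 mm as the range.

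**Similarity read as non-significance on one outcome.** Under equality, the chance that a two-sided 0.05 test is non-significant is 1 − 0.05 = 0.95, whatever the n or SD. The joint conditions were simulated (400,000 trials per scenario), because the 40% arm enters both contrasts. Results for n = 25 and SD 20 mm:

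| True state | 40% v 80% n.s. | and 40% beats LL | and 80% also beats LL (all of hypothesis 2) |
|---|---|---|---|
| BFR adds nothing | 95% | 2.0% | 0.5% |
| Only 80% LOP works, by 10 mm | 58% | 2.3% | 2.0% |
| Both levels better by 10 mm | 95% | 39% | 25% |
| Both levels better by 20 mm | 95% | 90% | 86% |

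The first column is the same when neither level works and when both do, so similarity alone does not discriminate. The second column does. With 21 per arm the first row is unchanged. For a 20 mm benefit, the 90% becomes 76% at SD 25 and 95% at SD 15.

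**Similarity read as equivalence within a margin.** Two one-sided 5% tests, n = 25, SD 20 mm, BFR adding nothing. The standard error is 20 × √(2/25) = 5.66 mm and the 90% half-width is 1.661 × 5.66 = 9.40 mm. Equivalence needs an observed difference smaller than the margin minus 9.40:

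- ±20 mm: 10.60 / 5.66 = 1.87 SE, met in 94%.
- ±15 mm: 5.60 / 5.66 = 0.99 SE, met in 68%.
- ±10 mm: 0.60 / 5.66 = 0.11 SE, about 8% by this shortcut and 10% by simulation, where the SD is estimated.

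At ±20 mm the rate is 75% for SD 25 and over 99% for SD 15. All these margins are illustrative. The 20 mm in Primary outcome measure is a minimal important improvement, not a tolerable difference between arms. Adding the condition that 40% beats LL brings the ±20 mm rate down to 2.0%.

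**The case against.** The sentences are Discussion prose in permissive language, not a formal decision rule, and they address which degree of BFR suits patients who cannot bear a high one. The operative claims are the hypotheses. Hypothesis 2 already joins superiority over low-load training with no difference between levels, and the LL arm is one of the groups in the mixed model, so its result will be visible. Formal interpretation criteria may also sit in an SAP that is not shown.

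Much of this stands. A reader might infer that the whole trial depends only on 40% v 80%, or that it would recommend 40% LOP in 95% of cases when BFR is useless. The documents do not support either. If all of hypothesis 2 governs the conclusion, the rate is about 0.5%. The 95% is just 1 − alpha under one assumed meaning of similar. The abstract speaks of outcomes in the plural, and non-significance on six independent outcomes (the main Discussion lists six) would give 0.95^6 = 74%, with correlated outcomes between 74% and 95%. A tight margin lowers the rate much further.

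What the objection does not remove is that the conclusion is stated twice without the LL condition, and that in the abstract it rests on a premise which the Background disputes. That is an inconsistency within the article, not a detail left to an SAP.

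**Conclusion.** The point holds as a defect in how the conclusion is stated. It is not tied to the first half of hypothesis 2, and the abstract and Background disagree on whether that half is already established. Similarity of 40% and 80% LOP alone cannot support choosing 40% LOP over the sham-cuff low-load programme.

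If BFR adds nothing, the stated condition is met in 95% of trials when similar means non-significant on one outcome. With a margin it is met in anything from 94% (±20 mm) to 10% (±10 mm) at an assumed SD of 20 mm and 25 per arm. Requiring 40% LOP to beat LL brings the non-significance figure to about 2%. The logical point does not depend on the SD, the margin or the definition of similar; only the equivalence rates and the power figures do. The design already contains the comparison needed. Nothing here bears on which cuff pressure is clinically right.

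**What to change.** In the abstract and in the main Discussion, make the conclusion conditional on two results: (1) 40% LOP BFR is superior to LL on the primary pain outcome, and (2) 40% LOP is similar to 80% LOP under a prespecified criterion. State that if (1) fails, similarity of the two levels gives no support for 40% LOP BFR over low-load training alone. Report 80% LOP v LL separately on its own contrast, since a failed 40% v LL comparison says nothing by itself about 80%. Reconcile the abstract with the Background on whether superiority of BFR over low-load training is established.

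No new arm, visit or participant is needed. The cost is a harder route to the favourable conclusion when the true benefit is small: at 10 mm (SD 20 mm, 25 per arm, similarity as non-significance) it is reached in about 39% of trials, against 95% for similarity alone. This mostly reflects the power of the 40% v LL contrast, which is about 42% at that benefit.

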**Trial registration:**

Chinese Clinical Trial Registry ChiCTR2000037859 (http://www.chictr.org.cn/edit.aspx?pid=59956&htm=4). Registered on 2 September 2020

## Background

Knee osteoarthritis (KOA) is one of the most common chronic musculoskeletal diseases. It can develop the deterioration in the subchondral bone, cartilage, synovium, and menisci [1], resulting in pain, stiffness, impaired functioning in daily activities, and a decline in the quality of life (QoL). According to an epidemiological survey, it is estimated that the prevalence of symptomatic radiographic KOA among older people is 12.1% in the USA [2] and 8.1% in China [3], and these figures are manifesting an upward trajectory. Due to its high prevalence, KOA may cause tremendous economic burdens on health services, such as conventional interventions and joint replacements [4]. Therefore, primary and secondary prevention programs are necessary to minimize social and personal costs.

Multiple risk factors may contribute to the development of KOA, such as age, sex, obesity, and joint factors; unfortunately, the link between these factors and KOA remains unclear [5–7]. Nevertheless, muscle weakness, especially in the quadriceps, is considered both a vital and a modifiable risk factor for KOA [8]. Previous studies have shown that muscle weakness is strongly associated with the incidence [8] and progression [9] of KOA, as well as the physical function and knee pain of individuals [10]. Moreover, muscle mass in the lower limbs is independently influenced by the presence of KOA [11] and related to the severity of symptoms in patients [12].

The main approach to improve muscle strength and mass is resistance training (RT). RT can decrease the risk of KOA by increasing muscle strength and muscular hypertrophy [13]. Based on the recommendations of the American College of Sports Medicine, a resistance load of 60–80% of an individual’s one-repetition maximum (1RM) is necessary to achieve muscle hypertrophy and improvements in muscular strength [14]. However, high-load resistance training (HLRT) can aggravate pain and joint deterioration in patients [15], resulting in decreased compliance to therapeutic exercises and a slower rehabilitation process.

Blood flow restriction (BFR) training has drawn the attention of clinicians and physiotherapists in the field of musculoskeletal rehabilitation, as it is believed to be an alternative approach to HLRT. In brief, a pneumatized cuff or tourniquet is used to block partial arterial blood flow to the limb, and this is combined with 20–30% 1RM low-load resistance training (LLRT). By creating a state of ischemia in the limbs, BFR training will produce a stronger physiological metabolic stress that includes growth hormones [16, 17] and increased recruitment of type II muscle fibers [18]. Thus, even though the load is relatively low during BFR training, it can still bring increases in muscle strength and mass, similar to the results obtained by HLRT. More importantly, BFR training requires a lower external load, which is beneficial in decreasing the joint loading and tolerance of RT.

Previous studies have found that BFR combined with LLRT yields better improvements in muscle strength compared with LLRT alone in patients with a risk of KOA [19, 20], while its effectiveness in increasing muscle strength, muscle mass, and function in patients with KOA is similar to that of HLRT [21, 22]. Nonetheless, it remains unclear whether the degree of BFR will influence the effectiveness of BFR with LLRT. Many factors contribute to the degree of BFR, including systolic blood pressure, diastolic blood pressure, sex, limb circumference, limb length, and cuff width [23, 24]. The application of limb occlusion pressure (LOP) can produce a more precise degree of arterial occlusion for different individuals compared with absolute air pressure. Only one previous trial has used the percent of LOP to identify the pressure for BFR training in patients with KOA [22]. Notably, 70% LOP BFR training has a similar effect in increasing muscle strength, quadriceps muscle mass, and function compared with HLRT. However, it has been shown that BFR pressures with 40% LOP are as effective as 80% LOP [15] in the acute response of muscles. Nonetheless, the ability to achieve a chronic response with BFR remains unclear, especially for patients with KOA. Additionally, while a higher LOP promotes more pain during exercise with BFR training [25], it seems that pressure with 40% LOP may be more comfortable for individuals compared with 80% LOP, making it beneficial in eliciting compliance to the intervention program.

It has shown in previous studies that the effectiveness of BFR with LLRT is not conclusive compared with LLRT alone [26]. For instance, Ferraz et al. demonstrated that LLRT with BFR is more effective in relieving pain compared with LLRT alone [22], while another study suggested that there was no difference between the two approaches [19]. Therefore, in this study, we set a group of LLRT without BFR to investigate whether LLRT with lower LOP is more effective than LLRT alone. Due to the fact that health education constitutes a minimized intervention that is nonetheless important for KOA [27], we set health education as a control group for comparison with the other three groups. The aim of this study is to investigate the efficacy of LLRT with different degrees of BFR in patients with KOA. Our measures will include pain, self-reported function, physical functional performance, muscular strength, muscle thickness, and QoL. We will also observe any adverse events to verify the safety of BFR training during the study.

Hypotheses:
LLRT, LLRT with low BFR (40% LOP), and LLRT with high BFR (80% LOP) will all be more effective than health education.Both LLRT with 40% BFR and 80% BFR will be more effective than LLRT alone, but there will be no difference between the two levels of BFR.

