### Outcome measures

#### Primary outcome measure

Pain

A VAS will be used to evaluate pain intensity at rest and under maximum situations during the last week. The VAS comprises a line with a length of 100 mm, in which “0 mm” corresponds to no pain and “100 mm” to the worst pain imaginable [40]. The VAS depicts pain effectively and is easily operated and widely applied in patients with KOA. The VAS will be evaluated at baseline and 12 and 24 weeks after the randomization of the participants. Notably, the minimal clinically important improvement for pain is about 20 mm/100 mm [41].

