### Statistical analyses

All data will be expressed as mean ± standard deviation (SD). A linear mixed model with repeated measures will be run to assess the data for fixed factors of the trial (LL group, High BFR group, Low BFR group, and HE group) and time (primary and secondary outcomes). Additionally, two-way ANOVAs will be used to analyze the differences between baseline, post-intervention, and follow-up measurements. Data from all subjects will be included in the statistical analyses, and the ITT approach will be applied to avoid disrupting the randomization of groups from dropping out through the trial. Any subject who started treatment will be included in the final outcome analysis regardless of whether he/she completed the study. Additionally, the missing data will be multiply imputed using chained equations with predictive mean matching, imputing data for each group separately. Estimates from 10 imputed data sets were combined using Rubin’s rules [54]. The level of significance will be set at *P* < 0.05 for all data. Statistical analyses will be performed using SPSS 22.0 (SPSS Inc., Chicago, USA).

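### The hypothesis that 40% and 80% LOP do not differ has only a difference test at P < 0.05 behind it, so the plan cannot verify it, and a moderate deficit for 40% LOP could pass unseen

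*Protocol article*

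**What the plan says.** - Protocol article, Background, Hypotheses: the second hypothesis expects both BFR arms to be better than low-load training alone, "but there will be no difference between the two levels of BFR".
- Abstract, Discussion: the practical message is conditional on similarity: "If a 40% LOP for BFR could produce similar clinical outcomes as an 80% LOP for BFR", the lower pressure can be chosen for patients who cannot bear the higher one. The main Discussion repeats this: "resistance using a lower LOP can be a good choice for those who are unbearable for high degree of LOP".
- Statistical analyses: "A linear mixed model with repeated measures will be run to assess the data for fixed factors of the trial", and time, with two-way ANOVAs in addition. The only decision rule is "The level of significance will be set at *P* < 0.05 for all data".
- Primary outcome measure: the one clinical benchmark is that "the minimal clinically important improvement for pain is about 20 mm/100 mm". It is not tied to the 40% v 80% comparison.
- Sample size estimation: repeated-measures ANOVA, four groups, three measurements, effect size 0.38, alpha 0.05, power 95%. This gives at least 84 participants, raised to 25 per group for 15% dropout. The section says this number is what is needed to verify the hypotheses for the primary outcomes.

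The article states no equivalence or non-inferiority margin, and no rule that compares a confidence interval with one.

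**The concern.** One clause of the hypotheses asserts sameness, and a treatment choice rests on it. A difference test can reject sameness but cannot support it. Under the stated rule the only outcome that looks like confirmation is P > 0.05, which becomes more likely as the samples shrink or the data get noisier.

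The sample size sentence makes this worse. It says the planned number verifies the hypotheses, but the calculation concerns the detection of some difference among four arms. What is at stake is a published statement that 40% LOP does as well as 80% LOP, resting on absence of evidence.

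**Working it through.** **1. The plan's own figure.** Inputs from Sample size estimation: k = 4 groups, m = 3 measurements, f = 0.38, alpha = 0.05, power 0.95. The correlation between measurements is not given; 0.5, the software's default, is assumed.

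For the between-groups F test, lambda = N·f²·m / (1 + (m − 1)·rho). At N = 84: 84 × 0.1444 × 3 / 2 = 18.19, with 3 and 80 df, and power is 0.952. At N = 80 it is 0.941. So 84 reproduces. The other repeated-measures options do not give it: within factors needs 20, and the group-by-time interaction needs 28. Dropout: 84 / 0.85 = 98.8, so 99, or 25 per group. The stated N is therefore sized for an omnibus test of four groups and says nothing about how alike two of them are.

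**2. Precision of 40% v 80% LOP.** Assumptions, none of them in the document: VAS SD of 15, 20 or 25 mm; correlation of baseline with week 12 of 0.5; baseline-adjusted comparison of the two arms. n is 21 (25 less 15%) or 25 (no information lost).

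SE = SD·√((1 − 0.5²)·2/n), df = 2n − 3, half-width = t(0.975, df)·SE.

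Example, SD 20, n = 21: SE = 20·√(0.75 × 2/21) = 5.35, and the half-width is 2.02 × 5.35 = 10.8 mm.

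**3. Chance of P > 0.05 when 40% LOP is truly worse** (noncentral t with noncentrality = deficit/SE):

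| SD (mm) | n per arm | Half-width (mm) | 10 mm worse | 15 mm worse | 20 mm worse |
|---|---|---|---|---|---|
| 15 | 21 | 8.1 | 32% | 5% | <1% |
| 15 | 25 | 7.4 | 24% | 2% | <1% |
| 20 | 21 | 10.8 | 55% | 22% | 5% |
| 20 | 25 | 9.9 | 48% | 15% | 2% |
| 25 | 21 | 13.5 | 69% | 41% | 17% |
| 25 | 25 | 12.3 | 64% | 33% | 11% |

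**4. What the planned N could show about similarity.** Two one-sided tests at 5%, true difference zero. Success means that the 90% CI lies inside ±M.

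| SD (mm) | M = 15 mm, n = 21 to 25 | M = 10 mm, n = 21 to 25 |
|---|---|---|
| 20 | about 74 to 83% | about 17 to 29% |
| 25 | about 43 to 56% | about 1 to 4% |

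For non-inferiority at a one-sided 2.5% level with zero true difference, power at margin M equals the power to detect a difference of M, which is one minus the entry in step 3. At 10 mm that is 45 to 52% for SD 20 and 31 to 36% for SD 25.

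For 80% non-inferiority power at 10 mm, n = 2·0.75·SD²·(1.96 + 0.842)²/10². This is 48 per arm at SD 20 and 74 at SD 25. The 10 and 15 mm margins are illustrations only.

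**The case against.** **The analysis plan is not shown and may hold a margin.** Detail can be left to it. But the article itself fixes the hypothesis, the significance rule and the basis of N, and asserts that N verifies the hypotheses. The objection is to what is stated.

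**The benchmark is borrowed.** The 20 mm figure is given as a minimal important improvement, not as a tolerable difference between arms. This stands: it can serve as an outer reference, but it does not supply the margin.

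**The clinical use is narrow.** The lower pressure is suggested for patients who cannot bear the higher one. For them the more relevant question may be 40% LOP against low-load training alone, which is a superiority question that the design does address. This narrows the harm. It does not remove the defect, because both the abstract and the Discussion word the conclusion as conditional on similarity.

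**A stronger reading is tempting.** A reader might infer that the trial would endorse 40% LOP even if it were clearly worse, or that non-significance is likely over a wide range of true differences. The figures do not support this. A deficit of the full 20 mm is missed in at most 17% of trials in the table. Even a 15 mm deficit is detected more often than not, and at SD 15 so is a 10 mm deficit. Nor does any section say that P > 0.05 will be reported as no difference; that is only the sole route the stated rule leaves open.

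**Conclusion.** The point holds in a bounded form. The plan states a hypothesis of no difference, rests a practical conclusion on similarity, claims an N that verifies it, and supplies only difference tests. That mismatch is logical and does not depend on any assumed SD.

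Its size does depend on assumptions. With SD 20 to 25 mm, correlation 0.5 and 21 to 25 per arm, a 10 mm deficit is non-significant in about 48 to 69% of trials (24 to 32% at SD 15), a 15 mm deficit in 15 to 41%, and a 20 mm deficit in 2 to 17%. Moderate deficits are at real risk of being missed; large ones mostly are not.

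The superiority hypotheses and the omnibus calculation are not called into question here. Which pressure suits which patient is not a matter for this review.

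**What to change.** Amend the protocol before analysis:

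1. State that P > 0.05 will not be read as similarity. Report the baseline-adjusted week-12 difference between 40% and 80% LOP in VAS pain with its 95% CI, and name which VAS item is used, since the outcome section lists pain at rest and at maximum.
2. Prespecify a between-arm margin, justified clinically and smaller than the quoted 20 mm improvement. Claim equivalence only if the 90% CI lies inside it, or non-inferiority only if the one-sided 97.5% bound does. Otherwise report the comparison as inconclusive.
3. Reword the second hypothesis to match. Limit the sample size statement to the omnibus comparison, and say that 100 participants give limited power for similarity.

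If no margin can be justified, item 1 alone is the minimum, and no similarity claim should then be made.

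Cost: no new patients or data. It takes an amendment, with the notices to participants, ethics committee and registry that the data management section requires; the Trial status section describes recruitment as still in progress. The price is a real chance of an inconclusive result. Good power at a tight margin would need more participants than planned.
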